### Concealment mechanism {16b}

The automated nature of the randomization process precludes any external influence on its outcome. Hence, there is no possibility to manipulate the allocation.

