### Who will take informed consent? {26a}

UPlusE participants are required to install one of the aforementioned apps on their smartphones in order to take part. Pregnant individuals will be recruited and enrolled by participating gynaecologists, and parents will be recruited and enrolled by paediatricians. Enrolment is achieved through a digital signing of the consent form and data protection declaration within the practice apps. A comprehensive patient information document precedes the consent form. The consent forms are then digitally transmitted to the project management for documentation and compliance with retention obligations.

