## Assignment of interventions: allocation

### Sequence generation {16a}

Following the confirmation of physicians’ participation in UPlusE, practices are randomly assigned to either the intervention or the control group (cluster randomization). The confirmation and randomization processes take place automatically within the practice app administration (opt-out regulation), with separate procedures for gynaecologists and paediatricians. The allocation to the groups is maintained at a 1:1 ratio, ensuring an equal distribution of 50% of physicians to both the intervention and control groups. To achieve this, randomization lists are generated in advance by the evaluation team using statistical software SAS 9.4 (TS Level 1M7 Copyright © 2016 by SAS Institute Inc., Cary, NC, USA) employing the method of simple random sampling (proc surveyselect). Participating practices are included in these randomization lists. To maintain a balanced ratio of intervention to control practices within regions, the inclusion in the list is organized by postal code. The automated nature of the randomization process precludes any external influence on its outcome.

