### Implementation {16c}

Each participant in a given practice will be designated to either receive the intervention or serve as part of the control group based on the practice’s assignment.

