## Assignment of interventions: blinding

### Who will be blinded {17a}

Due to the interventional nature and the cluster-randomized design, blinding of nurses, physicians, and participants is not possible. They will become aware of their randomization status. Hence, this is an open, randomized study.

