## Statistical methods

### Statistical methods for primary and secondary outcomes {20a}

The intervention in UPlusE will be scientifically evaluated using a multidimensional approach and various methods (multilevel analyses, process analyses, secondary data analysis) that, in combination, allow for a comprehensive assessment of different aspects of the project.

All data analyses will be conducted using pseudonymized data. After the observation period (U6), the primary and secondary endpoints for parents with psychological and psychosocial issues will be analysed in a group comparison (comparison between the intervention and the control group). Multilevel analyses will be conducted based on the intention-to-treat principle.

Additionally, the trajectory of values and the utilization of services for parents without psychological and psychosocial issues at the time of project inclusion (clinical evaluation) will be descriptively analysed. Quantitative parameters will be analysed using multilevel analyses to correct for cluster randomization. In the case of structural inequality between the intervention and control groups, relevant parameters (such as age, gender, number of pregnancies and births, partnership, socioeconomics—education, occupation, financial situation, severity of depression) will be adjusted for. All tests will be two-tailed with a significance level of alpha = 0.05.

In the analysis, a descriptive evaluation (e.g. symptom severity, child symptoms, service utilization) will be conducted for the group of parents who were positively screened. At the time of U6, a comparison between the intervention and control groups will be performed (e.g. symptom severity, parent–child bonding, child symptoms). Furthermore, across groups, psychosocial stress, depressive symptoms, stigma, and service utilization will be assessed.

The data from the process analysis questionnaires will be analysed descriptively and inferentially.

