### Interim analyses {21b}

After the recruitment phase is completed, baseline assessments will be performed. Particularly relevant here is the analysis of structural equivalence among participants from the intervention and control practices.

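### The concealment statement covers practice assignment only: parents are enrolled later by unblinded physicians, and adjustment for baseline differences depends on observed imbalance

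*Protocol article*

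**What the plan says.** On the timing of randomisation, section {16a} states: "Following the confirmation of physicians’ participation in UPlusE, practices are randomly assigned to either the intervention or the control group (cluster randomization". This process runs automatically inside the practice app administration. Concealment mechanism {16b} rests on that automation alone and concludes "Hence, there is no possibility to manipulate the allocation".

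Participants come in later and by another route. Under Who will take informed consent? {26a}, "Pregnant individuals will be recruited and enrolled by participating gynaecologists, and parents will be recruited and enrolled by paediatricians". On implementation, section {16c} states: "Each participant in a given practice will be designated to either receive the intervention or serve as part of the control group", according to the practice's assignment. For nurses, physicians and participants, Who will be blinded {17a} says "They will become aware of their randomization status. Hence, this is an open, randomized study".

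Three provisions bear on comparability:
- Interim analyses {21b} plans baseline assessments after recruitment: "Particularly relevant here is the analysis of structural equivalence among participants from the intervention and control practices".
- Statistical methods {20a} makes adjustment conditional: "In the case of structural inequality between the intervention and control groups, relevant parameters" are adjusted for. The examples given include age, gender, socioeconomic items and severity of depression.
- The missing-data section {20c} says inverse probability weighting may become necessary if baseline differences are significant.

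The Discussion names possible selection bias from app use and German language. It does not mention enrolment that differs by arm.

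**The concern.** In a cluster trial that recruits after randomisation, concealing the practice sequence does not protect the composition of the arms. Whoever invites parents influences who enters, and here that person works in an open practice.

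The exposure is specific to this design. Trial design {8} identifies positively screened parents as the relevant comparison, and the primary outcome is self-reported use of support. A physician in an intervention practice can offer a parent with a positive screen feedback and counselling on the result. A control physician receives no screening result before U6, apart from the safety alerts. If that difference affects who is invited or who agrees, the positively screened groups may differ in their tendency to seek help before any intervention effect.

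The plan's response depends on seeing an imbalance first. A significance trigger has limited power for a modest imbalance, and it makes the primary model depend on the data. The prognostic variables closest to the problem are collected, but their use in the primary model is not fixed in advance.

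**Working it through.** **Order of events, from the text**

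1. A physician confirms participation and the practice is randomised ({16a}).
2. That practice's physicians recruit and enrol parents ({26a}).
3. Each parent takes the practice's arm ({16c}).
4. Staff and participants are not blinded ({17a}).

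Step 1 is concealed by automation. Nothing in {16b} concerns step 2. Section {17a} says staff will become aware of their status without saying when. Because the arms' procedures differ from the first screen, knowledge of the arm at recruitment is a strong inference, but it is not stated.

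**The plan's own figure**

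Inputs from Sample size {14} and {20a}: 15% against 25%, two-sided alpha 0.05, power 0.80, 1:1.

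n per arm = [1.960·√(2·0.20·0.80) + 0.842·√(0.15·0.85 + 0.25·0.75)]² / 0.10² = 250, so 500 in total, as stated. Then 500 × 1.725 / 0.80 = 1078, as stated. The effective size behind the planned power is therefore 250 per arm.

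**Sensitivity to a shift b in underlying use (b is assumed; the documents give no value)**

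Use would be 15% in the control arm and 15% + b in the intervention arm, with no true effect. With p̄ the mean of the two rates, SE₀ = √(2·p̄(1−p̄)/250) and SE₁ = √[(p₁(1−p₁) + p₂(1−p₂))/250]:

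rejection rate = Φ[(b − 1.96·SE₀)/SE₁] + Φ[(−b − 1.96·SE₀)/SE₁].

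For b = 0.02: SE₀ and SE₁ are both 0.0328, giving Φ(−1.351) + Φ(−2.571) = 0.088 + 0.005 = 0.094.

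For selection the other way, the last column gives power when a true 10-point effect is masked by b, that is 15% against 25% − b.

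| b (points) | Rejection rate, no true effect | Power, selection in reverse |
|---|---|---|
| 0 | 5% | 80% |
| 1 | 6% | 72% |
| 2 | 9% | 63% |
| 3 | 15% | 52% |
| 5 | 31% | 31% |

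**Can a significance trigger see it?**

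Assume a prognostic trait with 40% use among those who have it and 10% among those who do not. A prevalence of 16.7% reproduces the plan's control rate: 0.167 × 0.40 + 0.833 × 0.10 = 0.15. The same two-proportion formula gives:

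| Prevalence in the two arms | Bias in use | Detected at 250 per arm | Detected at 539 per arm |
|---|---|---|---|
| 16.7% vs 21.7% | 0.05 × 0.30 = 1.5 points | 29% | 55% |
| 16.7% vs 26.7% | 0.10 × 0.30 = 3.0 points | 78% | 98% |

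The last column is the most favourable case for a check among positively screened parents: all 1078/2 = 539 per arm, with no clustering in the trait. A large imbalance would probably be seen. The smaller one would be missed in roughly 45% to 71% of trials.

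**The case against.** **The sentence in {16b} is not false.** Practices are the only units allocated and each parent inherits the practice's arm, so there is no individual allocation to manipulate. This stands. A reader might infer that the protocol misstates its concealment. What the text supports is that the statement is incomplete, because it is the whole answer on concealment and is silent on enrolment.

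**The plan does look at comparability.** It is tempting to say that selective enrolment goes unmeasured. The documents do not support that. Section {21b} plans a structural-equivalence analysis by arm, {18a} collects history of mental health problems at enrolment, the screening scores are taken from inclusion, and severity of depression is already among the examples for adjustment. What remains is the conditional trigger.

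**The motive is weaker than it looks.** Under {11b}, control parents with clinical signs of a problem are also encouraged to seek support, so a physician need not enrol a parent in order to help. The same section describes systematic screening of all parents. This is fair, and it leaves both the direction and the size of any selection unknown. A reader might infer a bias in favour of the intervention; the documents do not establish one.

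**Enrolment detail may sit elsewhere.** Counts of parents eligible, approached and declining may be in the full protocol, so their absence from an article is not a fault. The adjustment rule is different, because the article states it.

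**Adjustment cannot reach motivation.** Enrolment scores and history do not measure readiness to seek help. That is true, and it is a reason to state the limitation as well as to adjust.

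**Conclusion.** The point holds in a limited form. The assurance in {16b} is sound for practices and does not extend to the enrolment of parents, who are recruited after randomisation in an open design. Differential enrolment is therefore possible, in either direction and of unknown size. The planned baseline check helps, but making adjustment depend on observed inequality, and weighting on significance, can leave a modest prognostic imbalance uncorrected in the positively screened comparison.

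The figures show sensitivity and do not estimate this trial's error rate. They rest on the shifts and trait prevalences assumed above, on a normal approximation, and on the 250 effective subjects per arm implied by the plan's own design effect. A larger effective size would make a given shift more likely to produce a false positive, and would also make an imbalance easier to detect.

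**What to change.** 1. In {16b}, limit the statement to the assignment of practices, and say that participants are recruited after randomisation in an open design.
2. Replace the conditional rules in {20a} and {20c} with a primary multilevel model that always adjusts for prespecified enrolment values: EPDS, KID-PROTEKT and history of mental health problems, whatever imbalance is observed. Keep the equivalence analysis as description and not as a trigger.
3. Report the number enrolled and the proportion screening positive at enrolment, by practice and arm.
4. In the Discussion, name differential recruitment by arm as a limitation beside app use and language, and say that adjustment cannot remove unmeasured differences such as readiness to seek help.

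The cost is small. All of these variables are already collected, recruitment procedures do not change, and the reporting adds one table. The change should be made before outcome data by arm are examined, and communicated to the ethics committees and the registry as {25} provides.

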### Implementation {16c}

Each participant in a given practice will be designated to either receive the intervention or serve as part of the control group based on the practice’s assignment.

## Assignment of interventions: blinding

### Who will be blinded {17a}

Due to the interventional nature and the cluster-randomized design, blinding of nurses, physicians, and participants is not possible. They will become aware of their randomization status. Hence, this is an open, randomized study.

### Procedure for unblinding if needed {17b}

A procedure for unblinding is not applicable due to the open design.

## Data collection and management

### Plans for assessment and collection of outcomes {18a}

The following questionnaires will be used:Socio-demographic questionnaire:Upon study enrolment, comprehensive socio-demographic data will be collected, including age, gender, number of pregnancies and births, history of previous mental health issues, partnership, education, occupation, and financial situation.Edinburgh Postnatal Depression Scale (EPDS):The Edinburgh Postnatal Depression Scale (EPDS), an internationally validated screening instrument for depression [23], will be used. The scale consists of ten self-reported items about depressive symptoms. An EPDS total score of ≥ 10 points indicates a moderate probability of depression, while a score of ≥ 13 points indicates the presence of depression with high sensitivity and specificity [24], also suggesting the presence of anxiety disorders. In UPlusE, an adapted and pilot-tested version of EPDS (EPDS+) [25] will be employed.

The adapted version contains three more questions (‘Plus questions’):Have you ever experienced violence? Yes, quite often. Sometimes. Barely. Never.The birth of my child I experienced as…: Fulfilling. Okay. Unexpectedly difficult/with complications. Traumatizing.I have experienced my pregnancy (so far) as: Burdensome/tense. Rather burdensome/tense. Rather positive/relaxed. Positive/relaxed.

The ‘Plus questions’ do not influence the EPDS score, rather they can be interpreted as a short screening for traumatic experiences in addition to the screening for depressive symptoms [25].

3.KID-PROTEKT:The KID-PROTEKT questionnaire [3] will be used as a measuring instrument for parental psychosocial burdens. The questionnaire includes six items about personal stress situations. A score ≥ 1 is considered a basis for conversation to determine if there is a need for support .4.Postpartum Bonding Questionnaire (PBQ):Additionally, the scale 1 (impaired bonding) of the Postpartum Bonding Questionnaire (PBQ) with 12 items will be used. Overall, the PBQ is a simple and well-validated instrument for assessing impaired parent-to-child bonding. The scale 1 is a general factor that signals the likelihood of a relationship problem at a threshold (cutoff value) of 12 points [26]. Responses to each of the 12 items will be given on a 6-point Likert scale (‘always’, ‘very often’,
‘quite often’, ‘sometimes’, ‘rarely’, and ‘never’) [27].5.Questionnaire on Crying, Feeding, and Sleeping (SFS):For measuring infant regulatory disorders, the extended SFS questionnaire will be used, comprising 37 items about infant crying, sleeping, and eating behaviour [28]. Total mean scores above 1.84 (crying and sleeping) or above 1.27 (feeding scale) indicate regulatory problems. Six items based on DC: 0–5 (classification system for the diagnosis of mental disorders in infants, toddlers, and preschool children) will be used for further differentiation and clinical classification of symptoms related to excessive crying, sleep disorders, and early childhood feeding disorders.6.Questionnaire on treatment/counselling utilization:Utilization of treatment for mental health issues and counselling for psycho-social stress and parent-child bonding issues will be systematically captured via a project-specific questionnaire in the practice apps ‘My Gynaecology Practice’ and ‘My Paediatric Practice’ through self-report by the participants. The questionnaire assesses information about whether treatment/counselling has been sought. If utilization has occurred since the previous assessment, details such as the institution visited (pregnancy counselling centre, child protection coordination centres, ‘Early Prevention’ services, specialized outpatient clinic, psychiatrist/psychosomatics/psychotherapist, general practitioner, other), the motivating factor, and the referrer will be collected. As of our knowledge, specifically fitting standardized, validated, and publicly published questionnaires for this purpose are currently not available.7.Process analysis questionnaireTo identify technical and organizational barriers as well as facilitating factors for the implementation of the care model, a process evaluation will be conducted. This involves surveying all participating practices, mental health practitioners, and counselling services. Except for mental health practitioners and ‘Early Prevention’, the survey will be conducted using project-specific questionnaires via the practice apps ‘My Gynaecology Practice’ or ‘My Paediatric Practice’. Mental health practitioners and ‘Early Prevention’ services cannot be reached through the practice apps: for the process evaluation, these recipients will be invited to participate in the survey via email by the responsible contact persons from the study team. The survey will use a digital form. The questionnaires for process evaluation will be designed by the Institute for Community Medicine, University Medicine Greifswald, and will cover aspects such as:The number of participating practices, mental health practitioners, and ‘Early Prevention’ services.Their reasons for participation.The feasibility of implementing the intervention in their respective settings.Acceptance of the intervention.Perceived technical and/or organizational barriers or gaps in the implementation of the intervention.Benefits perceived by the involved practices, mental health practitioners, and ‘Early Prevention’ services due to the intervention,Factors promoting the implementation of the care model.

The various aspects will likely be queried using five-point Likert scales ranging from ‘Strongly disagree’ to ‘Strongly agree’ or ‘Not at all satisfied’ to ‘Completely satisfied.’

### Plans to promote participant retention and complete follow-up {18b}

UPlusE is a module of a special health insurance care program (BKK Starke Kids) not only offering clear advantages in healthcare but also leading to legally binding obligations at least for BKK-insured individuals. With UPlusE, the obligation entails committing to their treating doctor for the duration of the care and filling out the questionnaires in the practice apps. The number of questionnaires per time will stay within reasons and will approximately take 10–15 min. Participants can submit their answers only after all questions have been answered. To further remind and support the participants, a weekly note is sent via push message, e.g. how can I talk to my baby, etc. UPlusE will also be open to insured individuals from other insurers.

### Data management {19}

The data collected from the questionnaires through the app are managed in a secure and protected data management system. The telemedical service provider (Monks Ärzte im Netz GmbH) will regularly send pseudonymized datasets to the evaluator. These data will be entered into a database. The recruitment numbers will be closely monitored. To visualize the monitoring of recruitment numbers, recruitment graphics will be generated, indicating the recruitment status compared to the target state. Additionally, the data will undergo regular plausibility checks to proactively address any potential incompleteness, double data entries, implausibility, or systematic errors. This can involve adjustments to the user interface, informational materials, or training for the involved gynaecologists and paediatricians. The results of the recruitment monitoring and plausibility checks will be reported to the consortium leadership in a report format.

### Confidentiality {27}

The project is currently hosted on servers that are accessible directly from the internet. The servers are operated in an ISO 27001-certified data centre in Germany and are accessible only to selected personnel of the telemedical service provider. Patient data is encrypted using current encryption methods in accordance with the technical guideline TR-02102–1 of the Federal Office for Information Security (BSI), ensuring that only doctors and patients can access this information. The medical data collected from the questionnaires will be pseudonymized and forwarded to the evaluators only after explicit consent from the patients.

### Plans for collection, laboratory evaluation, and storage of biological specimens for genetic or molecular analysis in this trial/future use {33}

In UPlusE, no biological samples will be taken, and no laboratory tests will be conducted. Only data through questionnaires will be collected.

## Statistical methods

### Statistical methods for primary and secondary outcomes {20a}

The intervention in UPlusE will be scientifically evaluated using a multidimensional approach and various methods (multilevel analyses, process analyses, secondary data analysis) that, in combination, allow for a comprehensive assessment of different aspects of the project.

All data analyses will be conducted using pseudonymized data. After the observation period (U6), the primary and secondary endpoints for parents with psychological and psychosocial issues will be analysed in a group comparison (comparison between the intervention and the control group). Multilevel analyses will be conducted based on the intention-to-treat principle.

Additionally, the trajectory of values and the utilization of services for parents without psychological and psychosocial issues at the time of project inclusion (clinical evaluation) will be descriptively analysed. Quantitative parameters will be analysed using multilevel analyses to correct for cluster randomization. In the case of structural inequality between the intervention and control groups, relevant parameters (such as age, gender, number of pregnancies and births, partnership, socioeconomics—education, occupation, financial situation, severity of depression) will be adjusted for. All tests will be two-tailed with a significance level of alpha = 0.05.

In the analysis, a descriptive evaluation (e.g. symptom severity, child symptoms, service utilization) will be conducted for the group of parents who were positively screened. At the time of U6, a comparison between the intervention and control groups will be performed (e.g. symptom severity, parent–child bonding, child symptoms). Furthermore, across groups, psychosocial stress, depressive symptoms, stigma, and service utilization will be assessed.

The data from the process analysis questionnaires will be analysed descriptively and inferentially.

In addition to the quantitative analysis of utilization, gathered through self-report questionnaires in the app, utilization of healthcare services within the healthcare system and the associated costs triggered by utilization will be descriptively analysed based on billing data from participating health insurance company. Initially, the utilized services will be examined, followed by an examination of the costs of the services used. For the participating health insurance company, the costs of provided services are billed by healthcare providers. These costs are visible in the billing data, which can differentiate between total costs, costs for outpatient and inpatient services, and medication costs. All three participant groups (parents with psychological and/or psychosocial issues in the intervention and control group, as well as parents without psychological and/or psychosocial issues) will be compared in this regard. Both routine data for psychiatric/psychotherapeutic and somatic conditions of parents and their children will be analysed (inpatient and outpatient treatments, emergency responses, medications).

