### Sample size {14}

The proportion of all parents who avail themselves of any mental health services is based on the available figures. (18% [22], health insurance data: 10–12%) and is assumed to be 15% in the following. The assumption is that through the intervention, the proportion of affected parents using mental health services can be increased to at least 25% in the intervention group. With *α* < 0.05 and a power of 0.80, a sample size of 500 subjects is therefore required. The cluster-randomized controlled design must be considered when calculating the required number of participants. The design effect due to cluster randomization is estimated at 1.725 (intra-cluster correlation (ICC): 0.15; number of patients/practices: 2.5). With a dropout rate of 20%, the number of required positively screened subjects is (500 × 1.725) / 0.80 = 1078. Given a known prevalence of peripartum depression of 10–15% as the condition that is in our focus, a total of 10,000 parents (5000 each in the intervention and control groups) must be screened and included (Fig. 3).

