### Methods in analysis to handle protocol non-adherence and any statistical methods to handle missing data {20c}

As this is a study in a healthcare setting and not a clinical trial testing a clinical procedure or medication, protocol non-adherence is not relevant here. For intention-to-treat analyses, it may become necessary to impute missing data because the intention-to-treat analysis includes all participants, regardless of their adherence to the study. If (potentially multiple) imputation of missing data will be required, it will be carried out especially in the analysis of the primary research question. Scores will be imputed, not individual items, and this will be done separately for each outcome or research question. For per-protocol analyses, missing data will not be a concern, as only participants who have completed all necessary measurements will be considered here. If significant group differences will occur at baseline, the inverse probability weighting procedure may become necessary.

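### Observed baseline differences, not a rule fixed in advance, decide whether the primary comparison is unadjusted, covariate-adjusted or weighted

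*Protocol article*

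**What the plan says.** Section {20a} of the protocol article plans multilevel analyses by intention to treat, comparing the arms among affected parents. Covariates enter only on a condition: "In the case of structural inequality between the intervention and control groups, relevant parameters" are to be adjusted for. The parameters are given as examples (demographic, obstetric, partnership and socioeconomic items, and depression severity), so the list is open. No threshold for inequality is stated.

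Section {20c}, on non-adherence and missing data, adds a second conditional step: "If significant group differences will occur at baseline, the inverse probability weighting procedure may become necessary". It does not say which analysis the weighting serves, or how it relates to the adjustment in {20a}.

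Section {21b} places the check after recruitment has finished: "Particularly relevant here is the analysis of structural equivalence among participants from the intervention and control practices".

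On allocation, section {16a} randomises gynaecological and paediatric practices separately by simple random sampling, and states: "To maintain a balanced ratio of intervention to control practices within regions, the inclusion in the list is organized by postal code". Practices are allocated once physicians confirm participation. Section {17a} says that physicians and participants will know their arm, and section {26a} has the practices enrol participants themselves.

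Two obvious predictors of utilization are already collected. Table 1 lists the EPDS from inclusion onwards for all participating parents, and section {18a} records previous mental health problems at enrolment.

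**The concern.** Three different primary estimates are possible under the published text: unadjusted, regression-adjusted and weighted. Which one is reported depends on what the baseline table shows, and the two triggers are worded differently. In an open trial this leaves the choice of model to be made after arm-level data have been seen.

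The trigger is also the wrong guide. The size or significance of a baseline difference says nothing about whether the covariate predicts utilization. A strong predictor that happens to be balanced is left out, although including it would sharpen a risk difference. A weak predictor that happens to be unbalanced is put in. Because practices know their arm when they recruit, a genuine shift in severity between the arms is possible. A non-significant shift can still distort an unadjusted estimate.

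**Working it through.** **1. The plan's own figure.** Inputs from section {14}: control utilization "is assumed to be 15% in the following"; the intervention proportion "can be increased to at least 25% in the intervention group"; "and a power of 0.80, a sample size of 500 subjects is therefore required". From {20a}: "All tests will be two-tailed with a significance level of alpha = 0.05".

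Per arm, with mean proportion 0.20:
n = [1.96 × √(2 × 0.20 × 0.80) + 0.8416 × √(0.15 × 0.85 + 0.25 × 0.75)]² / 0.10²
= (1.1087 + 0.4723)² / 0.01 ≈ 250, so 500 in total.

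Then 500 × 1.725 / 0.80 = 1078.1, printed as 1078. Both figures reproduce with the design effect of 1.725 taken as printed. (Whether 1.725 follows from its stated inputs is a separate question.) The calculation assumes no gain from covariates, so the adjustment rule does not make 1078 wrong.

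**2. The conditional rules side by side.**

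| | {20a} | {20c} |
|---|---|---|
| Trigger | structural inequality, no threshold | significant baseline differences |
| Remedy | adjustment, will be done | weighting, may be needed |
| Variables | open list of examples | not named |
| Priority between the two | not stated | not stated |

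**3. How often a significance trigger misses a real shift (illustrative).** Take 250 effective subjects per arm, since 1078 × 0.80 / 1.725 ≈ 500 in total. Assume a true severity difference of d standard deviations between arms. Then z = d / √(2/250) = d / 0.0894.

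| Assumed d | z | Chance that a two-sided 5% test misses it |
|---|---|---|
| 0.10 | 1.12 | about 80% |
| 0.15 | 1.68 | about 61% |
| 0.20 | 2.24 | about 39% |

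If severity correlated 0.4 with a continuous outcome (assumed), a missed shift of 0.15 SD would leave 0.4 × 0.15 = 0.06 SD in the unadjusted estimate, about two-thirds of its standard error of 0.089.

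**4. Precision and type I error (illustrative).** Simulation with a continuous outcome, one covariate, N = 500, no clustering and 8000 replicates. The triggered rule adjusts only if baseline p < 0.05.

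| Assumed covariate–outcome correlation | SE unadjusted | SE always adjusted | Variance saved | Type I error of triggered rule |
|---|---|---|---|---|
| 0.2 | 0.089 | 0.088 | about 4% | 4.5% |
| 0.4 | 0.089 | 0.082 | about 16% | 4.9% |
| 0.6 | 0.089 | 0.072 | about 36% | 3.8% |

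The trigger fired in about 5% of replicates, so most of the saving is lost. The documents give no covariate–outcome correlation, so the actual saving cannot be derived. The table carries over in direction to a marginal risk difference, but not to a log odds ratio.

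**5. Specialty and entry point.** Section {26a} has gynaecologists enrol pregnant individuals and paediatricians enrol parents. Section {13} gives the entry points as pregnancy, U3, U4 or U5. Entry point therefore determines specialty, and a model containing both terms would be perfectly collinear.

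**The case against.** The strongest defence is that adjustment is sensible here. Participants enrol after allocation, real imbalance can arise, and the plan says it will respond to it. That stands: the fault lies in the trigger, not in the adjustment. It can also be said that an article condenses, and that an analysis plan not shown may hold the detail. That covers detail left out, but the conditional rule itself is published text. One could read the weighting sentence in {20c} as serving only the per-protocol or missing-data analyses, but nothing there limits it to them.

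Four stronger readings are tempting and not supported.

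- **That specialty and region are left out of the model.** The list in {20a} is open and no section excludes them. Region is only an ordering of the list under simple random sampling; its groups are not defined.
- **That the primary model would change by chance in 37% of trials.** Counting nine parameters in {20a}, 1 − 0.95⁹ = 0.37. This borrows the word significant from {20c}, applies it to the list in {20a}, and assumes independence, which is implausible for education, occupation and finances. It also assumes perfectly balanced recruitment, which is itself in doubt.
- **That the p-values are invalid.** The simulation shows 3.8% to 4.9%, which is no inflation and is conservative with a strong covariate.
- **That omitting covariates widens every confidence interval.** The article names no logistic model. If one were used, adding a predictor would generally not shrink the standard error of the log odds ratio. It would move the conditional odds ratio away from the null, so the trigger would change what is being estimated.

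**Conclusion.** The point holds in a limited form. Sections {20a} and {20c} leave the choice among three versions of the primary comparison to observed baseline differences, with two unlike triggers and no rule for choosing between the remedies. This follows from the text and needs no assumption.

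The consequences are a primary estimate that is not fixed in advance, a trigger that can miss a real severity difference, and precision forgone for a marginal risk difference. The 39% to 80% miss rates rest on the assumed shifts and on 250 effective subjects per arm. The 4% to 36% variance savings rest on assumed correlations and a continuous, unclustered analogue. Neither range estimates what will happen in this trial. Inflated type I error is not shown, and the sample size is unaffected. The point is worth correcting because the remedy is cheap, but it does not undermine the design.

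**What to change.** Replace the conditional sentences in {20a} and {20c} with one primary multilevel model, used whatever the observed balance and fixed before comparative data are examined:

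- arm and a practice random effect;
- enrolment EPDS score;
- history of mental health problems;
- parent's gender;
- entry point (pregnancy, U3, U4 or U5), which already carries the separate gynaecology and paediatrics randomisation, so specialty is not added as well;
- region, only if the postal-code groups used in randomisation are defined.

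Report the effect as a marginal risk difference. Keep the check in {21b} as description and drop baseline significance tests as a trigger. Retain inverse probability weighting as a named sensitivity analysis.

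The cost is one paragraph and no new data. Without region, the covariates use about six degrees of freedom if history and gender are each coded in two levels: 1 for EPDS, 1 for history, 1 for gender and 3 for entry point. Region would add a number that cannot be stated until its groups are defined.
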